## Methods and analysis

### Study protocol

This is a multicentric, prospective, observational cohort study involving three French academic hospitals (University Hospital of Angers, University Hospital of Tours and Regional Hospital of Orleans). Study patients will enter the cohort after they have been diagnosed with cardiac ATTR, including ^99m^Tc-PYP scintigraphy (grade 2 or 3) (20–22), according to the diagnostic algorithm for cardiac ATTR proposed by Gillmore et al., after they meet inclusion/exclusion criteria (Table 1).

**TABLE 1 T1:** Inclusion and exclusion criteria.

Inclusion criteria	Exclusion criteria
● Patients aged from 18 to 90 years	● Other heart failure cause (not ATTR)
● Understanding and speaking French ● With TTR amyloid cardiomyopathy (ATTRxt or ATTRm) confirmed by the association of: ⚬ clinical heart failure (NYHA I-III) ⚬ with echocardiogram and/or magnetic resonance imaging suggesting/indicating cardiac amyloidosis, ⚬ grade 2 or 3 99mTc PYP or bone scintigraphy, ⚬ and negative biological findings (i.e., serum immunofixation, urine immunofixation, serum free light chain assay), or, if one of those criteria is not met, amyloid deposits on biopsy specimens (from cardiac and non-cardiac sites), ● Intention to treat (Tafamadis)	● New York Heart Association (NYHA) class IV heart failure. ● Light-chain amyloidosis ● Liver or heart transplantation history ● Glomerular filtration rate below 25 mL per minute per 1.73 m^2^ of bodysurface area (Cockroft) ● High liver transaminase levels (two times the upper limit of the normal range) ● Severe malnutrition defined by a modified body-mass index (mBMI: serum albumin level in grams per litter multiplied by the conventional BMI) of less than 600; ● Concurrent treatment with non-steroidal anti-inflammatory drugs, tauroursodeoxycholate, doxycycline, calcium-channel blockers, digitalis, or ticagrelor ● Previous treatment with tafamidis or patisaran ● Previous CAD, severe epicardial stenosis with revascularization or ticagrelor treatment, coronary artery bypass grafting, myocardial infarction ● Contra-indications to pharmacological stress testing MPI: severe hypotension (<90 mmHg of Systolic arterial pressure), atrioventricular block 2nd or 3rd grade, carotid stenosis (unilateral > 70%, bilateral > 50%) ● Pregnancy ● Breastfeeding ● Protected adults

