**FIGURE 1 F1:**
[figure not shown]
Flow of the participants throughout the study. MBF, Myocardial Blood Flow; MFR, Myocardial Flow Reserve.

Potential participants referred for ATTR bone or PYP scan will be pre-screened by the nuclear medicine physician. After confirmation of TTR cardiac amyloidosis diagnosis, including ^99m^Tc-HDP or ^99m^Tc-PYP scintigraphy (grade 2 or 3) (20, 22, 23) according to the diagnostic algorithm for cardiac ATTR amyloidosis proposed by Gillmore et al., patients will be included and Tafamidis introduced, according to the guidelines. The treatment will be fully reimbursed by health insurance in this indication.

We estimate that the recruitment will take around 12–24 months. Participants will not receive any financial or non-financial incentives.

Patients will be included before the baseline dynamic CZT-SPECT myocardial perfusion imaging (with MBF and MFR), after written consent. Dynamic SPECT imaging protocol is displayed in Figure 2. All acquisitions will be performed on the same system: Discovery NM530c cardiac CZT cameras (General Electric Healthcare, Haifa, Israel) in all departments. The radiopharmaceutical used will be either ^99m^Tc-tetrofosmin for Orleans and Tours, and ^99m^Tc-mibi for Angers. Initial injection of 37 MBq will be used to center the patient’s heart in the field of view. Rest dynamic acquisition will then be performed with an injection of 250MBq of ^99m^Tc radiopharmaceutical, then flushed by 50 mL of saline to ensure consistent delivery of a tight bolus. Stress will then be induced using either a regadenoson (400 μg) injection or a dipyridamole perfusion (0.56 mg/kg), immediately followed with a 500MBq of ^99m^Tc radiopharmaceutical injection at hyperemia peak. Dynamic SPECT data will be reconstructed using Corridor 4DM™ software (INVIA, Ann Arbor, MI, United States) on a Xeleris workstation (General Electric Healthcare, Haifa, Israel).

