### Trial outcomes

The primary outcome is the variation of stress and rest MBF and MFR assessed by dynamic SPECT, between baseline and 24 months after Tafamidis treatment.

The secondary outcomes are:

•Results from baseline dynamic SPECT, confirming the stress and rest MBF and MFR reduction in cardiac ATTR patients,•Results from echo/MRI.

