With this study, we aim to demonstrate an impact of Tafamidis on microvascular dysfunction. Regarding our secondary endpoint, various perspectives can be seen. Firstly, the absence or low proportion of microcirculatory dysfunction in patients with cardiac amyloidosis. However, the sample size remains small, and the evaluation may be too early compared with the diagnosis (although often late); this is therefore a possible limitation of our study, which may explain the failure to find this microcirculatory dysfunction. The second option is a high proportion of microcirculatory dysfunction in patients with cardiac amyloidosis. Our hypothesis would then be confirmed and will therefore be in line with the study of Dorbala et al. performed in PET (4). Other studies also found microcirculatory dysfunction in these patients, as well as in other infiltrative heart diseases such as sarcoidosis (30), which reinforces the probability of this option.

Regarding the variation in MFR values after treatment, the first possibility is a significant decrease of MFR. In this case, the primary hypothesis of an improvement in microcirculatory dysfunction after treatment with Tafamidis would then not be verified. Thus, the lack of effect of Tafamidis on microcirculatory damage would be considered, and the benefits on overall survival, quality of life and cardiovascular events mentioned in the previous studies would probably be due to another pathophysiological process. However, an aggravating factor of Tafamidis on microcirculatory function could not be raised in our study in the absence of a “control” population (untreated or benefiting from another treatment), so another study with this objective could be envisaged, in order to distinguish the natural evolution of the pathology from a treatment effect.

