We might also consider a significant improvement of MFR after treatment. This would confirm a potential pathophysiological mechanism of the clinical improvement obtained by Tafamidis. It would then be interesting, in a second study, to evaluate whether this improvement in coronary microcirculation occurs early, within the first 12 months. Indeed, there is a need for biomarkers to predict the response to Tafamidis. Some will not respond to therapy; Monteiro et al. built a model to predict responsiveness to Tafamidis (31). They identified that disease severity, sex, and native TTR concentration at the outset of treatment were the most relevant predictors of response to Tafamidis. Plasma Tafamidis concentration after 12 months of therapy was also a predictor of response for male patients. Falk et al. suggested that measurement of TTR level change post-Tafamidis might be a surrogate for stabilization and could be an accurate measure of drug efficacy (32). Other treatments such as RNA interference therapeutics are developing rapidly in this indication with, it seems for the moment, great efficacy (17). So, the idea of a biomarker, possibly early, of efficacy would make it possible to quickly orient patients labeled as non-responders toward a switch to another therapy or to an association (combo RNAi and Tafamidis).

Finally, we might also envisage a lack of significant change in MFR values between 0 and 24 months. Our primary hypothesis would be untested. The potential limitations of our study would be a too short follow-up, or a too small sample.

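### A significant fall in MFR is read as lack of Tafamidis effect and a significant rise as confirming a potential mechanism, but the no-control caveat is applied only to harm

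*Protocol article*

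**What the plan says.** **Design.** The Study protocol section states: "This is a multicentric, prospective, observational cohort study involving three French academic hospitals". Under Interventions and participant timeline, after the diagnosis is confirmed, "patients will be included and Tafamidis introduced, according to the guidelines". There is no untreated or otherwise treated group. The Trial outcomes section states: "The primary outcome is the variation of stress and rest MBF and MFR assessed by dynamic SPECT, between baseline and 24 months after Tafamidis treatment". For the analysis, the Statistical analysis plan section compares continuous variables with a two-tailed paired t-test and expects 50 patients, without a sample-size calculation.

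**Aim.** The Discussion says: "With this study, we aim to demonstrate an impact of Tafamidis on microvascular dysfunction". The abstract likewise says that the effect of Tafamidis will be assessed.

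**Stated readings of the result (Discussion).**
- Significant fall in MFR: the hypothesis of improvement is not borne out, "the lack of effect of Tafamidis on microcirculatory damage would be considered", and the drug's benefits in earlier studies would probably come from some other process.
- Significant rise in MFR: "This would confirm a potential pathophysiological mechanism of the clinical improvement obtained by Tafamidis".
- No significant change: "Our primary hypothesis would be untested", with short follow-up or a small sample named as possible limitations.

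**Caveat (same paragraph as the first reading).** The article says that "an aggravating factor of Tafamidis on microcirculatory function could not be raised in our study in the absence of a" comparison group, and that a further study could be envisaged to tell natural evolution from a treatment effect.

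**The concern.** A before-after comparison in patients who are all treated estimates one quantity: natural course plus drug effect plus anything else that changed over 24 months. The article recognises this, but uses it only to block a conclusion of harm. If natural course cannot be separated from drug effect, a fall does not point to lack of effect any more than to harm, and a rise does not confirm a mechanism of the drug.

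A drug that slows a progressive process without reversing it could have its microvascular benefit set aside because MFR still fell. An improvement with non-drug causes could be reported as support for a drug mechanism. The Discussion goes on to link a rise to the idea of an efficacy biomarker for directing non-responders to other therapy, so a misattributed change could carry beyond this paper.

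**Working it through.** The article states no figure for this point, so there is none to reproduce. The check is a comparison of its statements, followed by an illustration.

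**1. What the comparison estimates.** For each patient, observed change = natural course + drug effect + other influences. The paired test addresses only whether the mean of this sum is zero. With no control group, no term can be isolated.

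**2. The caveat set against each reading.**

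| Result | Stated reading | Does the no-control reason apply? | Does the article apply it? |
|---|---|---|---|
| Significant fall | harm | yes | yes |
| Significant fall | lack of effect | yes | no |
| Significant rise | potential mechanism confirmed | yes | no |

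**3. A fall is compatible with benefit.** The Current knowledge section describes the placebo-controlled phase 3 result partly as a reduced decline in functional capacity and quality of life. Those are not MFR, so carrying the pattern over is an analogy. It does show that benefit as slowed worsening is the form the article itself cites.

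**4. A rise has other possible sources.** These include other care, regression to the mean and selective survival. On the last, the same section gives deaths in 78 of 264 treated patients (29.5%), and a paired comparison uses only patients scanned twice. If that proportion held here (an assumption, as populations and follow-up differ), 50 × (1 − 0.295) ≈ 35 pairs would remain.

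**5. Illustration of how often the readings would mislead.** The article gives no SD of change, natural-course rate, effect size or alpha. Assume a paired t-test at two-sided 5%, with d = mean change / SD of change. Power comes from the noncentral t distribution with n − 1 degrees of freedom and noncentrality d√n.

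- Natural course d = −0.8 and a drug that halves it: net d = −0.8 × 0.5 = −0.4. P(significant fall) = 0.79 with 50 pairs and 0.69 with 40. The true drug effect is +0.4.
- Other net values with 50 pairs: d = −0.2 gives 0.28, d = −0.3 gives 0.55, d = −0.6 gives 0.99.
- Zero drug effect with a non-drug upward shift: d = +0.2 gives P(significant rise) = 0.28 with 50 pairs and 0.23 with 40; d = +0.4 gives 0.79 and 0.69.

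**6. The non-significant case.** The 95% CI half-width in SDs of change is t(0.975, n − 1)/√n:
- n = 50: 0.284
- n = 40: 0.320
- n = 30: 0.373

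A non-significant estimate lies within one half-width of zero, so the upper limit can be as high as 2 × 0.284 ≈ 0.57 SD (n = 50) or 2 × 0.373 ≈ 0.75 SD (n = 30). The interval says which improvements are excluded, and it may exclude few.

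**The case against.** The passages are Discussion text, not decision rules. The Statistical analysis plan section contains no such interpretation, and the wording is hedged: lack of effect would be considered, the mechanism is a potential one, the alternative process is only probable. The Study and aims section frames the hypothesis as improvement against baseline, so a fall does contradict the hypothesis as stated. The study is labelled observational and proof of concept, the missing control group is disclosed, patients with coronary disease are analysed apart, and diabetes data are collected. Calling a null result untested, next to sample size and follow-up, probably means inconclusive.

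Most of this stands, and it limits the severity. It does not remove the point. The hedges soften both readings, but neither carries the no-control caveat. Saying that a fall fails to support improvement from baseline is correct; going on to lack of drug effect is the step the design cannot support. Separate handling of coronary disease and collection of diabetes data do not supply an untreated comparison.

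Three stronger readings are tempting and not supported:
- *Any change in MFR is attributed to the drug.* The causal readings attach to significant changes. A non-significant one is put down to follow-up or sample size.
- *No result could count against the hypothesis.* The Discussion says that a significant fall would leave it unverified.
- *A modest observed fall would be read as lack of effect whatever its significance.* If untreated MFR fell by 0.30 and the drug halved this, the mean change would be −0.15. With 50 pairs an observed −0.15 is significant only if the SD of change is below 0.15/0.284 ≈ 0.53. Above that, it belongs to the inconclusive case.

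**Conclusion.** The concern holds as an inconsistency of interpretation, of moderate severity. The Discussion gives a reason why treatment effect and natural course cannot be separated here, applies it to harm alone, and leaves the lack-of-effect and mechanism readings without it. The aim of demonstrating an impact of the drug and the abstract's reference to its effect go further than a single-arm before-after comparison allows.

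This conclusion rests on the text and needs no assumed figure. The size of the risk does: under the stated assumptions with 50 pairs, a drug that truly slows decline would produce a significant fall with probability 0.28 to 0.99 as the net change runs from −0.2 to −0.6 SD. A reader might infer that the article would declare the drug inert or the mechanism proven; its hedged wording does not go that far. Endpoint, test and sample size are unaffected.

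**What to change.** - **Abstract and Discussion aim:** replace the assessment of a Tafamidis effect, and the aim to demonstrate its impact, with estimation of the within-patient change in myocardial blood flow and MFR over 24 months under Tafamidis. Say that this is not a treatment effect.
- **Discussion, fall in MFR:** keep the statement that improvement from baseline was not shown. Add that a fall is compatible with slowed progression, no effect or harm, and drop the inference that the drug's benefits come from another process.
- **Discussion, rise in MFR:** say that it is compatible with a drug effect but does not confirm one, and repeat the no-control caveat there.
- **Discussion, no significant change:** call the result inconclusive, and interpret it through the mean change and its 95% confidence interval, naming the improvements the interval excludes.

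The cost is wording and a weaker claim. No data collection, endpoint, test or sample size changes.

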## Ethics and dissemination

The trial will be performed in accordance with the recommendations guiding physicians in biomedical research involving human subjects, adopted by the 18th World Medical Association General Assembly, Helsinki, Finland and stated in the respective participating countries laws governing human research, and Good Clinical Practice. The protocol was approved by Orleans Hospital Research Committee (CHRO-2021-05) and by Sud-Mediterranée IV Regional Ethics Committee (21 06 02); current version in use is 3.0.

After the end of the trial, the collaborators will discuss the main results prior to publication. The scientific communications and reports corresponding to this study will be produced under the responsibility of the principal investigator coordinating the study with the agreement of the responsible investigators and will be submitted for publication in peer-reviewed journals. Manuscripts will be prepared, and authorship will be determined by mutual agreement.

## Ethics statement

The studies involving human participants were reviewed and approved by Sud-Mediterranée IV Regional Ethics Committee. The patients/participants provide their written informed consent to participate in this study.
